#### Analyses of secondary objectives

Using the model outlined in the Analysis plan section, Table 4 provides a summary of the endpoint, analysis population, statistical model, and resulting estimate for each of the secondary objectives.

**Table 4 Tab4:** Statistical approach to be used for secondary objectives

Objective	Endpoint	Analysis population	Model	Estimate
Secondary objective #1	Number of days from birth until the participant meets criteria for medically ready for discharge	ITT (FNAST infants only)	GLMM • Distribution: negative binomial • Link function: log	Similar to the Primary analysis of primary objective section
Secondary objective #2	Receipt of pharmacologic treatment	ITT	GLMM • Distribution: binary • Link function: log	Adjusted risk of receipt of pharmacologic treatment for NOWS in infants managed with a symptom-based dosing approach Adjusted risk of receipt of pharmacologic treatment for NOWS in infants managed with a scheduled opioid taper approach Adjusted relative risk of receipt of pharmacologic treatment for NOWS between infants managed with a symptom-based dosing approach to infants managed with a scheduled opioid taper approach
Secondary objective #3	Number of days from birth until hospital discharge	ITT	GLMM • Distribution: negative binomial • Link function: log	Adjusted mean number of days until hospital discharge in infants managed with a symptom-based dosing approach Adjusted mean number of days until hospital discharge in infants managed with a scheduled opioid taper approach Difference in the adjusted mean number of days until hospital discharge between infants managed with a symptom-based dosing approach and infants managed with a scheduled opioid taper approach Adjusted RR of days until hospital discharge between infants managed with a symptom-based dosing approach to infants managed with a scheduled opioid taper approach
Secondary objective #4	• Inpatient composite safety outcome • Inpatient critical safety outcome • Outpatient composite safety outcome • Outpatient critical safety outcome	ITT	Descriptive statistics	Percentage of infants who met each endpoint will be summarized by study intervention
Secondary objective #5	Number of doses of primary medication administered	ITT-PT (stratified by type of medication)	GLMM • Distribution: negative binomial • Link function: log	Adjusted RR of doses of primary medication administered between infants who were pharmacologically treated with a symptom-based dosing approach to infants who were pharmacologically treated with a scheduled opioid taper approach
Secondary objective #6	Receipt of secondary medications	ITT-PT	GLMM • Distribution: binary • Link function: log	Adjusted relative risk of receipt of secondary medication between infants who were pharmacologically treated with a symptom-based dosing approach to infants who were pharmacologically treated with a scheduled opioid taper approach
Secondary objective #7	Transitioned to an opioid taper due to persistent signs of withdrawal	ITT-PT1	Descriptive statistics	Percentage of infants who were initially pharmacologically treated with a symptom-based dosing approach but transitioned to an opioid taper due to persistent signs of withdrawal
Secondary objective #8	Cessation of opioid treatment due to excessive sedation	ITT-PT2	Descriptive statistics	Percentage of infants who were initially pharmacologically treated with a scheduled opioid taper approach but stopped treatment due to excessive sedation
Secondary objective #9	• Inpatient composite safety outcome • Inpatient critical safety outcome • Outpatient composite safety outcome • Outpatient critical safety outcome	ITT-PT	Descriptive statistics	Percentage of infants who were pharmacologically treated and who met each endpoint will be summarized by study intervention

Similar to the sub-group analyses performed for the primary objective outlined in the Primary analysis of primary objective section, sub-group analyses will also be conducted for each secondary endpoint to determine if the intervention effect within each assessment and management approach is modified by the study period in which the participant was born.

#### Descriptive analyses

Baseline characteristics will be compared between the following groups using descriptive statistics:Within the ITT population:◦ Participants managed for NOWS using the symptom-based dosing approach and participants managed for NOWS using the scheduled opioid taper approach◦ Participants included in the ITT-PT population and participants not included in the ITT-PT populationWithin the ITT-PT population:◦ Participants who were pharmacologically treated using the symptom-based dosing approach and participants who were pharmacologically treated using the scheduled opioid taper approach

Each nominal/categorical variable will be summarized within each group and overall using a frequency and a percentage. The distribution of each nominal/categorical variable will be compared between the groups using a Pearson’s chi-squared test or Fisher’s exact test (as appropriate). Interval or ratio scale variables will be summarized within each group and overall using a mean, standard deviation, median, and inter-quartile range. The distribution of each interval or ratio scale variable will be compared between the groups using a Wilcoxon rank sum test. All tests will be performed using a two-sided significance level of 0.05. No adjustment for multiple comparisons will be performed.

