### Stratification, randomization, and blinding/masking

Each study site (i.e., cluster) will be randomized in a 1:1 allocation ratio to one of two sequences, following a 5-week run-in:Scheduled opioid taper approach for 5 months (period 1) followed by a 3-week washout followed by symptom-based dosing approach for 5 months (period 2)Symptom-based dosing approach for 5 months (period 1) followed by a 3-week washout followed by scheduled opioid taper approach for 5 months (period 2)

The randomization scheme will be stratified by the assessment and management approach used at each study site (i.e., FNAST or ESC). Study sites will be notified of their allocated sequence following randomization.

Due to the nature of the study intervention, the protocol study team, site PI, site study team, and participants will be unblinded to the assigned study intervention.

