### Inclusion criteria

Sites who meet all of the following criteria are eligible to participate in this study:The site is willing and able to transition to a symptom-based dosing approach at a randomly allocated time and is willing and able to transition from a symptom-based dosing approach to a scheduled opioid taper approach at a randomly allocated time.The site uses either the Eat, Sleep, and Console care approach or the Finnegan Neonatal Abstinence Scoring Tool or modification thereof to assess infants with NOWS and will continue to use the same assessment and management approach throughout the study.The site provides scheduled opioid treatment with morphine, methadone, or buprenorphine for infants with NOWS and has an established algorithm for a scheduled pharmacologic taper prior to study initiation. The site agrees to maintain the type of opioid(s) used and use the study approved treatment algorithms throughout the study.

Individuals who meet all the following criteria are eligible for enrollment as study participants:The infant is ≥ 36 weeks’ gestation.The infant had antenatal opioid exposure identified by at least one of the following:◦ History of maternal opioid use during pregnancy◦ Positive maternal toxicology screen for opioids during the second or third trimester of pregnancy◦ Positive infant toxicology screen for opioids during the initial hospital stayThe infant is being assessed and managed for NOWS at an eligible study site.The infant is at risk for pharmacologic treatment for NOWS defined by either of the following:◦ At least 1 score ≥ 8 if assessed and managed with FNAST or modification thereof◦ At least 1 yes if assessed and managed with the ESC care approach

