### Measures to minimize bias

The following measures will be taken to minimize bias in this study:Due to the nature of the study interventions, site-specific effects may arise. Consequently, a cluster crossover study design was selected because each study site will administer both study interventions at randomly selected times, thereby allowing for within-site estimates of the intervention effect.The assessment and management approach (FNAST or ESC) used at each study site may substantially affect the outcomes of interest. To address potential confounding, each study site will be required to use the same assessment and management approach for the duration of the study. Additionally, the randomization scheme will be stratified by the assessment and management approach to ensure that the percentage of study sites using each assessment and management approach is similar between the two sequences.

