### Analysis plan

All statistical analyses will be performed by DCC biostatisticians. Data will be monitored for accuracy and completeness throughout the study. Analyses will only be performed after the database has been locked.

For descriptive summaries of study data, the following will be presented:Nominal/categorical measures will be summarized using frequencies and percentages.Interval or ratio scale measures will be summarized using means, standard deviations, medians, 95% confidence intervals (CIs), 25th and 75th percentiles, and ranges.Ordinal measures will be summarized depending on the number of levels. An ordinal measure with five levels or fewer will be summarized as a nominal measure. An ordinal measure with more than five levels will be summarized as an interval or ratio scale measure.

Unless otherwise specified, each objective will be addressed by fitting a generalized linear mixed-effects model (GLMM) specified with a distribution and link function appropriate to each participant-level outcome in infants with NOWS who are assessed and managed with FNAST and ESC separately. Each model will also include the following fixed effects:Dosing approach (symptom-based dosing approach or scheduled opioid taper approach)Study period in which participant was born (study period 1 or 2)

Random effects for site will also be included in the model to account for within- and between-period intra-cluster correlation. The form of the random effect for site will be evaluated by comparing information criteria across the models with different forms and selecting the form that produces the best fit. Small sample corrections will also be employed to account for the small number of sites that are randomized.

Because it is of clinical interest to separately evaluate all objectives in infants with NOWS who are assessed and managed with FNAST and ESC separately, no adjustment for multiple comparisons will be made.

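### Baseline characteristics are tested as if infants were independent, so the stated 5% level of those descriptive tests is not assured in this site-randomised trial

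*Protocol article*

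**What the plan says.** The Descriptive analyses section opens: "Baseline characteristics will be compared between the following groups using descriptive statistics". It lists three comparisons: by dosing approach in the ITT population, pharmacologically treated versus not treated within ITT, and by dosing approach in ITT-PT. Categorical variables are compared with Pearson's chi-squared or Fisher's exact test. For the others, "The distribution of each interval or ratio scale variable will be compared between the groups using a Wilcoxon rank sum test". The section then sets a level: "All tests will be performed using a two-sided significance level of 0.05". It names no term for site, period or assessment approach (ESC or FNAST).

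The Analysis plan section treats the modelled objectives differently: "Random effects for site will also be included in the model to account for within- and between-period intra-cluster correlation". It adds a fixed period effect, small-sample corrections, and separate fits for ESC and FNAST.

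Two further statements bear on why baseline balance is of interest. On masking, "the protocol study team, site PI, site study team, and participants will be unblinded to the assigned study intervention". On entry at ESC sites, an infant qualifies with: "At least 1 yes if assessed and managed with the ESC care approach".

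**The concern.** Infants at one site tend to resemble each other, and the site is the unit of randomisation. A test that takes each infant as an independent observation uses the wrong variance for the between-arm difference. In a cluster crossover the error can go either way. Each site serves in both arms, which cancels shared site effects. Any site effect that changes from one period to the next does not cancel.

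The stake is interpretive. Site staff know the allocation when they assess and identify infants, so randomising sites does not by itself ensure that similar infants enter both arms. The ITT-PT comparison is a subset formed after allocation, and the protocol's rationale section says the proportion treated may differ by approach. A reader of the baseline table will look for case-mix differences, and p-values at an uncertain level could give a false alarm or false reassurance.

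**Working it through.** **Inputs from the protocol.** 24 sites (16 ESC, 8 FNAST), 10 infants per site per period, exchangeable correlation, ICC 0.15, over-dispersion 5.5 (ESC) and 8.4 (FNAST), all from Sample size considerations. Treatment rates in the planning data: 39.1% (ESC) and 78.8% (FNAST).

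**Assumptions.** The ICC of 0.15 is for time to medically ready for discharge. No ICC is given for any baseline variable, so 0.05 to 0.15 is assumed. The ratio r of between-period to within-period correlation is 1 under the protocol's exchangeable structure; 0.8 and 0.5 are assumed alternatives.

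**Step 1: the design factor reproduces the plan's own power.** For a two-period cluster crossover with m infants per site-period,

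D = 1 + (m − 1)·ICC − m·ICC·r.

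With m = 10, ICC = 0.15, r = 1: D = 1 + 1.35 − 1.50 = 0.85. For ESC at 10.5 versus 8.3 days, the variance of the difference is 0.85 × 5.5 × (10.5 + 8.3)/160 = 0.549, so the standard error is 0.741 and the ratio is 2.2/0.741 = 2.97. On a t-distribution with 32 − 3 = 29 degrees of freedom, power is 81.8%. The same steps give 90.8% at 8.0 days for ESC, and 79.9% and 90.0% for FNAST (13 degrees of freedom). Table 5 states 80% and 90%, so the factor describes the design well.

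**Step 2: true size of a test that ignores site.** Such a test in effect sets D = 1. Its true two-sided size at nominal 5% is 2·[1 − Φ(1.96/√D)].

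| ICC | r | D | True size |
|---|---|---|---|
| 0.05 | 1 | 0.95 | 4.4% |
| 0.05 | 0.8 | 1.05 | 5.6% |
| 0.05 | 0.5 | 1.20 | 7.4% |
| 0.15 | 1 | 0.85 | 3.4% |
| 0.15 | 0.8 | 1.15 | 6.8% |
| 0.15 | 0.5 | 1.60 | 12.1% |

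The break-even is r = (m − 1)/m = 0.9, where D = 1 and the size is 5.0% at any ICC. At ICC 0.01 the size stays between 4.9% and 5.5% for r from 1 to 0.5.

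**Step 3: simulation of the tests named in the plan.** With 24 sites and ICC 0.15, the Wilcoxon test gave 4.1%, 6.4% and 12.5% for r = 1, 0.8 and 0.5 with equal site sizes. The protocol expects enrolment to vary by site. With an assumed coefficient of variation of 0.7 in site size, the figures were 5.1%, 10.3% and 16.9%. The chi-squared test moved the same way but less: 4% to 9% with equal sites and 6% to 13% with unequal ones.

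**Step 4: treated versus not treated.** Here the crossover gives no cancellation, because treated and untreated infants are unevenly spread over sites. With treatment rates of 39.1% and 78.8% and no within-site association, the Wilcoxon size was mostly about 6% to 11%, rising with the ICC, and reached about 14% in the least favourable setting at ICC 0.15.

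**Step 5: a test that respects the design.** Taking each site's period 1 minus period 2 mean and comparing these differences between sequences gave 4.3% to 5.5% in every between-arm setting run.

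**The case against.** The strongest reply is that these are descriptive tests. No efficacy conclusion, covariate choice or decision rests on them, and the planned summaries by arm let a reader judge balance without p-values. Under the protocol's own exchangeable correlation and equal site sizes the between-arm tests are slightly conservative, and clear inflation needs a loss of correlation between periods that the document does not state. The ICC of 0.15 may partly reflect site treatment practice; birthweight or sex may cluster less. All of this stands, and it keeps the point small. It does not remove it, because the section does prescribe hypothesis tests and a level.

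Stronger readings are tempting but unsupported:

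- A reader might infer that this table is the trial's only check on differential identification of infants. The protocol gives it no such role. Maternal race and ethnicity are recorded for all screened infants, and the full analysis plan is not shown. Waiver of consent and identification by record review also limit selective enrolment.
- A reader might infer that the plan models clustering for every outcome and departs from this only here. It does not: secondary objectives #4, #7, #8 and #9 are also summarised descriptively.
- A reader might infer a bias in the primary result from extra mild infants in one arm. That would be selection bias, which exists whichever baseline test is printed; the choice of test neither causes nor cures it.

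**Conclusion.** The point holds in a limited form. The named tests ignore site in a site-randomised trial, and their 5% level is not assured. For m = 10 and an assumed baseline ICC of 0.05 to 0.15, the between-arm size is about 3% to 4% with exchangeable correlation and equal sites, about 6% to 8% at r = 0.8 (about 10% at ICC 0.15 with very unequal sites), and about 7% to 17% at r = 0.5, the top figure again needing unequal sites. The treated versus not-treated test is at about 6% to 11% in most settings. Neither a definite direction nor a definite size can be claimed, because the baseline ICCs and r are not given. The consequence is confined to how case-mix balance is read, and the matter is minor.

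**What to change.** In Descriptive analyses, do one of two things:

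- Delete the unadjusted tests and the significance level, and report standardised differences by arm, separately for ESC and FNAST, beside the summaries already planned.
- If tests are wanted, replace them with the plan's own mixed model, with each baseline variable as outcome, dosing approach (or treated status) and period as fixed effects, a random site effect, and the small-sample correction already foreseen.

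The first is simpler and fits the descriptive label. Either needs only minor programming on data already collected. An analysis of infants enrolled out of those screened, by arm, could be informative, but it would be an addition and is not needed to correct this section.

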### Interim analyses

#### Interim analysis of efficacy data

Using the approach outlined in the Primary analysis of primary objective section, one interim analysis testing the efficacy of the study intervention on the primary endpoint will be performed when the assessment of the primary endpoint is completed in approximately 50% of enrolled infants with NOWS. To account for multiple tests conducted at the interim and final analyses, the nominal significance level that will be used at the time of the interim and final analyses will be determined using O’Brien-Fleming stopping boundaries via the Lan-DeMets approach. Further details will be provided in the SAP.

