### Recruitment

The protocol study team will screen interested sites for eligibility and will randomize eligible sites into one of two arms (see Fig. 1). With the proposed study design, all infants with NOWS cared for at each study site will be managed using the dosing approach assigned to the study site during one of the two study periods. There will be a 5-week run-in prior to the first study period. There will be a 3-week washout between the end of the first study period and start of the second study period where no infants will be enrolled. Study sites will transition their pharmacologic treatment approach per their randomized allocation during the 3-week wash out period. The inpatient clinical team will assess infants with antenatal opioid exposure and establish the diagnosis of NOWS. The initiation of clinical management for infants with NOWS will not be impacted by the study intervention. Non-pharmacologic care will be considered first-line treatment for all infants with NOWS at study sites and will be implemented and maximized per each study site’s usual approach. The site study team will identify potential participants based on their eligibility following review of the medical record after delivery.

Site recruitment and retention: The protocol study team began to optimize the potential for recruitment during initial protocol development through an assessment of potential study sites’ willingness to participate in and enthusiasm for various study designs. The study design chosen for this protocol incorporates feedback from potential sites. During the site assessment process, the protocol study team will expect each site to commit in writing to the site’s participation in and completion of the study with maintenance of the site’s allocated study intervention for the duration of the study. The protocol study team will facilitate retention of study sites through the focused allocation of funds to support participation, assessment of needs, provision of support, and troubleshooting at each study site, as needed.

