If 2 participants are accrued per site per month across the 24 sites, a total sample size of 480 participants would require 5 months per period. The duration of each period is expected to be 5 months; this length may need to be modified to ensure sample size is met in Finnegan and ESC groups. Additionally, due to variation in enrollment across the sites and that enrollment in each period will end at the same time across all sites, the number of infants enrolled in the study may be higher than 480.

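### At the planned accrual the efficacy interim falls at the end of period 1, before any site has crossed over, and holds about 18% of the final ESC information

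*Protocol article*

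**What the plan says.** All references are to the protocol article.

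- **Trigger and model.** Under Interim analysis of efficacy data, one look "will be performed when the assessment of the primary endpoint is completed in approximately 50% of enrolled infants with NOWS". It tests the primary endpoint with the method of the primary analysis. Significance levels are "determined using O’Brien-Fleming stopping boundaries via the Lan-DeMets approach", with further details left to the SAP. The Interim analyses section under Monitoring lets the DSMB recommend stopping early for efficacy on the result.
- **Accrual.** Sample size considerations plans as follows: "If 2 participants are accrued per site per month across the 24 sites", then "a total sample size of 480 participants would require 5 months per period". It adds that "enrollment in each period will end at the same time across all sites".
- **Washout.** Recruitment describes a 3-week gap between the end of the first period and the "start of the second study period where no infants will be enrolled".
- **Purpose of the crossover.** Measures to minimize bias says that each site gives both interventions, "thereby allowing for within-site estimates of the intervention effect".
- **Model.** Analysis plan specifies fixed effects for dosing approach and for study period (1 or 2), site random effects for within- and between-period correlation, and small-sample corrections. The primary hypothesis concerns ESC infants only.

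**The concern.** The trigger is a head count, and in a two-period crossover head count and information do not move together. The first period alone gives only a comparison between sites. Most of the precision comes from the second period, when each site becomes its own control. A look timed at half the infants therefore lands where the design is weakest.

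Two things are at stake. An efficacy stop could be recommended on the kind of comparison that the crossover was meant to improve on. And the interim analysis, run by the stated method at the stated time, cannot estimate every term of that method.

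**Working it through.** **Inputs** (Sample size considerations and Table 5): 16 ESC sites, 8 per sequence; m = 10 infants per site per period; ICC 0.15; exchangeable correlation, so the between-period ICC equals the within-period ICC (ratio r = 1); scheduled-taper mean 10.50 days; over-dispersion 5.5; two-sided 0.05; detectable relative rate (RR) 0.79 at 80% power.

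**1. Reproduce Table 5.** Outcome variance = 5.5 × 10.50 = 57.75. For the full crossover, Var(difference) = 2 × 57.75 × (1 − 0.15)/160 = 0.614, SE = 0.783 days. Detectable ESC means are 10.50 − (1.960 + 0.842) × 0.783 = 8.31 at 80% power and 10.50 − (1.960 + 1.282) × 0.783 = 7.96 at 90%. With variance proportional to each arm's mean and a t reference on 29 df they are 8.35 and 8.03. Table 5 gives 8.3 and 8.0, so the variance structure is the protocol's own.

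**2. Timing.** 2 × 24 × 5 = 240 = 50% of 480. In ESC sites, 2 × 16 × 5 = 160 = 50% of 320. Both are the whole of period 1 and none of period 2.

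**3. Information share.**
- Period 1 only: design effect 1 + 9 × 0.15 = 2.35 on 80 infants per arm. SE of the difference = √(2 × 57.75 × 2.35/80) = 1.84 days.
- Full trial: design effect 1 + 9 × 0.15 − 10 × 0.15 × r on 160 per arm, which is 0.85 at r = 1.
- Share = (0.85/160)/(2.35/80) = 0.85/(2 × 2.35) = **0.181**.

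| r (between/within-period ICC) | Share | Source of r |
|---|---|---|
| 1 | 18% | protocol (exchangeable) |
| 0.8 | 24.5% | assumption |
| 0.5 | 34% | assumption |

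With the observed ESC ICC of 0.1119 and r = 1 the share is 22%. With 15 infants per site per period (ICC 0.15, r = 1) it is 14%.

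**4. Boundary.** The two-sided Lan-DeMets O'Brien-Fleming spend is 4[1 − Φ(2.241/√t)].

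| Fraction t | Alpha spent | z |
|---|---|---|
| 0.50 | 0.00305 | 2.96 |
| 0.34 | 0.00024 | 3.67 |
| 0.245 | 0.000012 | 4.38 |
| 0.181 | 0.00000027 | 5.14 |

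Suppose the boundaries are set for t = 0.5 (2.963, then 1.969) and the true fraction is 0.181. A bivariate normal with correlation √0.181 gives an overall alpha of 0.0513.

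**5. Chance of crossing at RR 0.79.** On the log scale, interim SE = √[(5.5/10.5 + 5.5/8.3) × 2.35/80] = 0.187, and the expected z is 0.236/0.187 = 1.26.
- Boundary 2.96: 1 − Φ(2.96 − 1.26) = 4.5%. Using the 80%-power drift instead, 2.80 × √0.181 = 1.19, gives 3.8%. Crossing needs an observed RR of about exp(−2.96 × 0.187) = 0.575.
- Boundary 5.14: 1 − Φ(5.14 − 1.26) = about 0.005% (0.004% with the drift of 1.19).
- The interim SE does not involve r, so the 4% to 5% does not depend on it. Boundaries set at the true fraction for r = 0.8 and 0.5 give 1 − Φ(4.38 − 1.26) = 0.09% and 1 − Φ(3.67 − 1.26) = 0.8%.

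**6. If the look slips into period 2.** With a and b infants per site in the two periods, v₁ = 0.15 + 0.85/a and v₂ = 0.15 + 0.85/b. Information is proportional to (v₁ + v₂ + 0.30)/(v₁v₂ − 0.0225), or 1/v₁ if b = 0. Relative to (10, 10): (9, 1) gives 30%, (8, 2) 39%, (10, 1) 31%, (10, 2) 42% and (10, 3) 52%.

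**The case against.** **The SAP may settle it.** The section never equates half the infants with half the information. Lan-DeMets can use whatever fraction has accrued, and the details are deferred to the SAP. A reader might infer that the protocol spends alpha as if t = 0.5, but the text does not say so. This stands against any claim that the boundary is wrong as written. It does not rescue the trigger or the model, which the protocol itself states, and an SAP cannot supply period-2 data at the end of period 1.

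**Treatment is not confounded with site.** That inference is tempting because each site has used only one approach. But sites are randomized 1:1 to sequence within the ESC and FNAST strata, so period 1 is a valid parallel cluster comparison. It is imprecise, not confounded.

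**The model does not fail altogether.** With one period the period term drops out and the between-period component is not identifiable. The treatment effect and a site random intercept can still be estimated.

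**Harm is small.** Alpha inflation is about 0.001, and a mistaken stop is unlikely. The small-sample corrections lower the chance further: on a t reference with 14 df (an assumption), the threshold becomes an RR near 0.51 and the chance about 3%. This stands. It shows that the look is nearly inert, which is itself a reason to change it.

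**Timing is a plan, not a certainty.** Period length may be modified and enrolment may exceed 480, and sites switch approach during the washout while the last period-1 endpoints complete. A stop before any site had switched is therefore not established. With equal periods, however, the 50% point stays near the crossover.

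**Side issues.** The trigger counts ESC and FNAST infants together, but under the plan both strata reach 50% at once. The sentence "Analyses will only be performed after the database has been locked" might be read as forbidding an interim; the interim is expressly provided for, so this is a minor wording matter.

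**Conclusion.** The point holds as a timing and definition fault. At planned accrual the efficacy look comes when the ESC data contain no within-site contrast, two elements of the specified model cannot be estimated, and the information is about 18% of the final amount. That figure rests on the protocol's own 10 infants per site per period, ICC of 0.15 and exchangeable correlation, and on equal periods filled as planned. The 25% to 34% range rests on ICC ratios that the document does not give.

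The consequence is a look with little use. With a boundary set for t = 0.5 it is too lenient for the data, yet crosses only about 4% to 5% of the time at the planned effect. With a boundary set at the true fraction it almost never crosses. The documents do not support a claim of biased comparison or of material type I error inflation.

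**What to change.** In Interim analysis of efficacy data, and in the matching Interim analyses paragraph under Monitoring:

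1. Define the look by the information fraction for the ESC primary estimate from the final model, not by the count of all enrolled infants.
2. Time it after sites have accrued period-2 data. On the protocol's inputs, half the information is reached at about 10 + 3 infants per site, which is 13/20 = 65% of planned enrolment.
3. Compute the Lan-DeMets boundary at the fraction actually reached.
4. Bar an efficacy stop on period-1 data alone.

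Alternatively, drop the efficacy look, keep the DSMB safety review at that time, and test the final analysis at two-sided 0.05.

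Either way the change is wording in the protocol, the SAP and any DSMB charter. The first option costs a later look. The second gives up an early stop that had about a 4% to 5% chance at the planned effect.

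Trial status shows that enrolment began in March 2024. If the look has already taken place, report the information fraction, the model and the alpha actually used.
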